#### PRO Assessment Time Points

Prospective assessment of newly prescribed patients before and after treatment is required to assess changes in PROs over time. PROs will be completed at baseline before starting medicinal cannabis, at 2-3 weeks after starting medicinal cannabis (end of titration period), and then at 1, 2, 3, 5, 7, 9, and 12 months after the titration period.

The acceptable PRO assessment time windows are indicated in Table 1.

### Analyses and Statistical Considerations

#### Analysis Set

All analyses will be performed using SPSS software (version 26.0; IBM Corp). Baseline demographic and clinical data will be summarized descriptively for all patients registered for the study. Categorical data will be presented as frequencies and percentages. For continuous scale data, mean, SD, median, 25th and 75th percentiles, and minimum and maximum scores will be presented.

PRO analyses will explore changes over time using mixed linear models. Subgroup analyses will compare differences in PROs between underlying conditions, dose, and duration of pain and over time using linear mixed models.

#### Statistical Considerations

A comprehensive PRO-specific statistical analysis plan will be produced by the study statistician. The key considerations include the following:

PRO questionnaire responses will be scored into PRO scales for outcome analysis according to standard scoring algorithms provided by the questionnaire developers and custodians.Rates and reasons for missed PRO assessments will be summarized to assess likely missing data mechanisms against missing data assumptions of statistical modeling.For each PRO, all participants with a score for that PRO at baseline and at least one time point after starting medicinal cannabis will be analyzed.Linear mixed models will be used to compare groups in their PRO scores, adjusted for their PRO levels at baseline and with additional covariates such as duration of pain, previous cannabis use, use of other medications, and overall and prespecified subgroups.If the scores are highly skewed, a suitable transformation will be sought to achieve normality.As there are several PRO scales and time points and correlation among them is anticipated, statistical significance levels will be adjusted using an appropriate method [82].The clinical significance of differences in the PRO questionnaires will be interpreted using existing guidelines (eg, QLQ-C30) [83], maintaining the overall type 1 error at 5% or less.

Missing items within the PRO questionnaires are not expected. This is because of the web-based administration platform alerting participants of missed items and the requirement to complete those items before progressing to the next page. Only those participants who complete at least 2 questionnaires (baseline and one other) will be included in the analysis. Single missed assessments will be imputed using the last value carried forward technique, that is, no change from that individual’s last assessment. Pattern mixture models will be used to impute scores for missed assessments based on recorded reasons [84].

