#### Primary Objective

The primary objective of this study is to describe changes in the PROs (HRQL, pain, fatigue, sleep, anxiety, and depression) from baseline to 3 months for a large cohort receiving medicinal cannabis.

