#### Hypotheses

The study includes 3 hypotheses: (1) PROs will improve from baseline to 3 months in patients accessing medicinal cannabis, (2) improvements in PROs at 3 months will be maintained over a 12-month period, and (3) no differences in PROs will be observed between patients being treated for different conditions (eg, chronic pain, MS, epilepsy, Parkinson disease, or cancer).

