## Discussion

### Principal Findings

The results of this study will show whether PROs improve in patients accessing prescribed medicinal cannabis from baseline to 3 months and whether any changes are maintained over a 12-month period. This study will also identify whether there are differences in improvements in PROs among patients being treated for different conditions (eg, chronic pain, MS, epilepsy, Parkinson disease, or cancer).

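### Excluding participants with only a baseline makes the 3-month change describe those who returned a later form; separately, the between-condition contrast should be named

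*Protocol article*

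**What the plan says.** All places are in the protocol article.

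- **Analysis set.** Statistical Considerations gives the rule twice. Per outcome, "all participants with a score for that PRO at baseline and at least one time point after starting medicinal cannabis will be analyzed". Later in the same section: "Only those participants who complete at least 2 questionnaires (baseline and one other) will be included in the analysis".
- **Missing assessments.** The same section adds: "Single missed assessments will be imputed using the last value carried forward technique". It also plans pattern mixture imputation by recorded reason. As written, both operate within the restricted set and do not bring baseline-only participants back.
- **Primary question.** Primary Objective asks for the change "from baseline to 3 months for a large cohort receiving medicinal cannabis".
- **Model for change.** Analysis Set says only: "PRO analyses will explore changes over time using mixed linear models". No baseline covariate is mentioned there.
- **Model for groups.** Statistical Considerations says: "Linear mixed models will be used to compare groups in their PRO scores, adjusted for their PRO levels at baseline".
- **Group question.** Principal Findings promises to show "whether there are differences in improvements in PROs among patients being treated for different conditions", and the Abstract (Results) says much the same. Hypothesis 3 is worded differently: "no differences in PROs will be observed between patients being treated for different conditions".

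**The concern.** This is a single cohort, so no comparator can absorb a selection effect. The analysis rule conditions on something that happens after enrolment, namely returning a follow-up form. A person who fills in the baseline and then stops, whether for lack of benefit, side effects, illness or lack of interest, is left out of the primary result. If those people differ from the rest in baseline level or in response, the estimated mean change moves away from that of the cohort named in the objective. The article gives representativeness as a reason for the study, so this matters to its purpose. The exclusion is also unnecessary: a linear mixed model can use a baseline-only record when baseline is one of the responses.

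A second, separate issue concerns the comparison of conditions. Diagnosis groups are not randomised and may start at different levels. A baseline-adjusted contrast then answers a different question from a contrast of improvements, and the article uses the language of both.

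**Working it through.** **1. The plan's own figure.** Sample Size gives effect 0.1, two-sided 1% level, 95% power, 20% loss and N = 2142. For a paired comparison the normal approximation is ((2.576 + 1.645)/0.1)² ≈ 1782. The noncentral t gives 1785, and 1785 × 1.20 = 2142. The figure reproduces as a test of within-person change, so 0.1 is the yardstick for any bias in that change.

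**2. Assumptions.** The article does not give the baseline-only share, the correlation ρ between baseline and 3 months, or the dropout mechanism. Assumed: share 5, 10 or 20%; ρ = 0.5 or 0.7; score SD 1; true improvement 0.10 SD; dropout odds ratio (OR) 1.5 or 2 per SD. The 20% share is a ceiling, because it equals the whole planned loss and a baseline-only person must miss every form from T1 to T8.

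The yardstick is in SDs of change and the results below are in SDs of score. SD of change = √(2(1−ρ)), which is 1.00 at ρ = 0.5 and 0.77 at ρ = 0.7, so the comparison is direct in the first case and approximate in the second.

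**3. Estimated 3-month improvement** (simulation of 1,000,000; simulated truth 0.102 at ρ = 0.5 and 0.100 at ρ = 0.7). Each cell gives OR 1.5 / OR 2. Kept means that baseline-only records enter a likelihood model assuming missing at random (MAR).

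| ρ | Baseline-only | Worse baselines leave: excluded | Same: kept | Non-improvers leave: excluded | Same: kept |
|---|---|---|---|---|---|
| 0.5 | 5% | 0.092 / 0.085 | 0.102 / 0.102 | 0.122 / 0.135 | 0.116 / 0.127 |
| 0.5 | 10% | 0.082 / 0.069 | 0.102 / 0.102 | 0.141 / 0.168 | 0.132 / 0.152 |
| 0.5 | 20% | 0.062 / 0.038 | 0.102 / 0.102 | 0.180 / 0.229 | 0.161 / 0.199 |
| 0.7 | 5% | 0.094 / 0.090 | 0.100 / 0.100 | 0.116 / 0.126 | 0.113 / 0.122 |
| 0.7 | 10% | 0.088 / 0.080 | 0.100 / 0.100 | 0.131 / 0.151 | 0.126 / 0.144 |
| 0.7 | 20% | 0.077 / 0.062 | 0.100 / 0.100 | 0.161 / 0.200 | 0.152 / 0.186 |

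With dropout completely at random, exclusion returns the truth to within 0.001 throughout.

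Check on the baseline-dependent case: error = −(1−ρ) × m, where m is the mean standardised baseline of those retained. At 20% and OR 2 the error at ρ = 0.5 is 0.038 − 0.102 = −0.064, so m = 0.064/0.5 = 0.128. The formula then predicts −0.3 × 0.128 = −0.038 at ρ = 0.7, and the table gives 0.062 − 0.100 = −0.038.

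Error ranges from the table:
- Worse baselines leave: from 0.094 − 0.100 = −0.006 to 0.038 − 0.102 = −0.064.
- Non-improvers leave: from 0.116 − 0.100 = +0.016 to 0.229 − 0.102 = +0.127.
- What keeping the records recovers when non-improvers leave, at 20% and OR 2: (0.229 − 0.199)/0.127 = 24% of the error at ρ = 0.5, and (0.200 − 0.186)/0.100 = 14% at ρ = 0.7.

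**4. Between conditions.** Let two conditions differ by D at baseline and change equally. The contrast of changes is 0 and the baseline-adjusted contrast is (1−ρ)D. For assumed D = 0.25–0.8 and ρ = 0.5–0.8 this runs from 0.2 × 0.25 = 0.05 to 0.5 × 0.8 = 0.40 SD. At D = 0.5 and ρ = 0.6 it is 0.4 × 0.5 = 0.20 SD.

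With an assumed 200 per condition, SE = √(2/200 × (1 − 0.36)) × √(1 + 0.5²/4) = 0.0825, and 0.20/0.0825 = 2.42. A difference is then declared with probability about 0.44 at the 1% level and 0.68 at the 5% level.

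In the reverse case, where patients with equal baselines have equal expected follow-up whatever their condition, the adjusted contrast is about 0 and the contrast of changes is about −0.20 SD.

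**The case against.** Several points on the other side have force.

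- **The bias is conditional.** It is nil if early dropout is completely at random, and its sign depends on who leaves. This stands.
- **The high shares are unlikely.** One later form is enough to stay in the analysis, so the baseline-only share should be below the planned 20% loss. At 5% with baseline-dependent dropout the error is only about 0.006–0.017 SD. This stands, and the upper figures should be read as a ceiling.
- **Keeping the records helps little when non-improvers leave.** This also stands. The change of model alone is not a full remedy.
- **Population.** Baseline forms are completed before treatment, and the objective concerns people receiving it. Analysing everyone with a baseline could bring in people who never started. The fix has to allow for this.
- **Mitigation.** Rates and reasons for missed assessments will be summarised, and the site is asked for reasons after two consecutive misses. This will help to describe the problem, but the analysis rule still leaves those people out.
- **A full analysis plan is announced.** True, but this is not a gap left to it. The article states the exclusion, twice.

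Two stronger readings are tempting, and the article supports neither. A reader might infer that the baseline covariate itself biases the 3-month change. The covariate is stated only for comparing groups, and the sentence on change over time mentions none. A reader might also infer that baseline-adjusted differences between conditions are false. That holds only if the target is equal change. This is Lord's paradox: the two contrasts answer different questions, and each misleads as an answer to the other's. Hypothesis 3 speaks of differences in outcomes rather than in improvement, and Analysis Set also plans subgroup comparisons over time, so a condition-by-time contrast is not excluded.

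**Conclusion.** The point holds in two limited parts.

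First, the stated exclusion makes the primary change an estimate for people who returned at least one later form. That can bias it as an estimate for the cohort named in the objective. Under the assumed 5–20% baseline-only and a true improvement of 0.10 SD, the result is too small by about 0.01–0.06 SD if worse-baseline patients leave, and too favourable by about 0.02–0.13 SD if non-improvers leave. It is unaffected if dropout is completely at random. The upper ends are comparable with the 0.1 effect that the study is powered for; the lower ends are minor. The actual size cannot be known from the article.

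Second, for the comparison of conditions only, the article promises differences in improvement and specifies baseline-adjusted comparisons. With unequal starting levels and equal change these differ by (1−ρ)D, or 0.05–0.40 SD over the assumed range. The defect is that the article does not say which contrast answers hypothesis 3; neither model is wrong in itself.

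**What to change.** 1. **Analysis set.** In the primary mixed model, include every participant with a baseline score who started treatment or whose start is not ruled out.
2. **Primary model.** Treat T0 to T8 as repeated responses with time as a fixed effect, and estimate the primary result as the T4 minus T0 contrast.
3. **Sensitivity.** Step 2 removes the bias only under MAR. Extend the planned pattern mixture analysis to baseline-only participants, for example with a scenario in which they show no improvement. Report the baseline-only share and how those participants differ at baseline.
4. **Between conditions.** Report the condition-by-time contrast of changes alongside the baseline-adjusted contrast, and state in advance which one answers hypothesis 3.

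Cost: wording in the protocol and the forthcoming analysis plan, and a little more analysis work. The class of model stays the same and no new questionnaire data are needed. Treatment start must be established for baseline-only participants or left as not ruled out. The primary estimate will still rest on MAR, which is why step 3 belongs with it.

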#### Data Collection and Assessment

Study data will be recorded by physicians at recruitment sites on case report forms and by participants in the questionnaire booklets. These will be completed on the web through the University of Sydney research data capture system, REDCap [54].

Screening and registration and clinical data will be completed by the physician at the recruitment sites. The REDCap database will collect information only identifiable by REDCap-assigned study record ID numbers. Physicians at recruitment sites will maintain a record of participants’ study ID numbers for each screened and registered participant entered. Where required, data can be updated for individual participants by notifying the study project manager of the corresponding study ID numbers (eg, to record participant withdrawal). If 2 consecutive assessments are missed by participants, the study project manager will contact the physician at the recruitment site to determine the reasons for missed assessments, if known.

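### Single missed assessments are filled by last value carried forward, which sets change since the previous visit to zero in a study of change; the scope and role of the second imputation rule are not stated

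*Protocol article*

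**What the plan says.** Under Statistical Considerations the protocol article sets two imputation rules in consecutive sentences.

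- Rule 1: "Single missed assessments will be imputed using the last value carried forward technique", glossed as "that is, no change from that individual’s last assessment".
- Rule 2: "Pattern mixture models will be used to impute scores for missed assessments based on recorded reasons".

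Neither sentence says which rule belongs to the primary analysis, and rule 2 does not say whether it covers single misses. The same section plans linear mixed models and also states: "Rates and reasons for missed PRO assessments will be summarized to assess likely missing data mechanisms".

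The only route to reasons that the article describes is under Data Collection and Assessment: "If 2 consecutive assessments are missed by participants, the study project manager will contact the physician at the recruitment site". That contact is meant to establish why the forms were missed, so far as the physician knows. The questions added to follow-up forms (Follow-Up Data Collection) do not include the reason for a missed form.

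The primary objective is change from baseline to 3 months. The second hypothesis is that "improvements in PROs at 3 months will be maintained over a 12-month period".

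**The concern.** The study exists to describe change, and rule 1 assumes none since the last visit. With the visit order of Table 1, the rule does three different things:

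- A missed T1 receives the baseline, so a pre-treatment score stands as an on-treatment score.
- A missed T4, the primary time point, receives T3.
- A missed T8 receives T7. For each person filled, any change over that last interval is set to nil, which is what the maintenance hypothesis predicts.

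The filled value then enters the model as data, with no allowance for its being a guess. When a lone miss is followed by a completed visit, the later score is ignored in filling the gap. None of this is needed: a linear mixed model uses incomplete series directly if misses are at random given the observed scores.

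The second problem is the neighbouring sentence. As worded, one missed form could fall under both rules. If pattern mixture is meant to reach single misses, the article shows no way to obtain the reasons it needs. A missed T8 after a completed T7 can never trigger the query, because no later assessment exists to make a second consecutive miss.

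**Working it through.** **Plan's own figure.** For a paired change with effect size 0.1, two-sided 1% and 95% power, n = ((2.576 + 1.645)/0.1)² ≈ 1782, or 1785 with the noncentral t. Then 1785 × 1.2 = 2142, as stated. The missing-data rule does not enter this figure, so rule 1 neither supports nor undermines it.

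**Inputs not in the documents (assumed).** The share p filled by rule 1 at a visit (5% to 20%), the score course, the between-visit correlation, and who misses. Improvement is counted as positive.

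**1. Bias at T4, random misses.** Let D be the mean change from T3 to T4. A share p receives T3 in place of T4, so bias = −p × D.

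| p | D = +0.10 SD (still improving) | D = 0 (flat) | D = −0.04 SD (fading, 0.14 to 0.10) |
|---|---|---|---|
| 5% | −0.005 | 0 | +0.002 |
| 10% | −0.010 | 0 | +0.004 |
| 20% | −0.020 | 0 | +0.008 |

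**2. Against the precision.** With an assumed correlation of 0.6 between baseline and T4, the standard error of the mean change is √(2 × (1 − 0.6)/2142) = √(0.8/2142) ≈ 0.019 SD. At p = 20% and D = 0.10 the bias is about one standard error. A simulation with n = 2142, a course of 0.20 SD at T3 and 0.30 SD at T4, and correlations of 0.6 with baseline and 0.7 between T3 and T4 gave estimates of 0.290 and 0.280 at 10% and 20% random misses. Coverage of the 95% interval was about 92% and 83%.

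**3. Bias at T4, worse patients miss more.** Here carry-forward is biased even on a flat course, because patients who were low at T3 tend to move back towards the mean and the copied score does not. A simulation with true change about 0.10 SD, n = 1785, correlation 0.6 per visit step, and odds of missing T4 rising by e^0.5 ≈ 1.65 per SD worse at T3 gave:

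| Course | Carry-forward, 10% / 20% nominal missing | Likelihood-type estimate |
|---|---|---|
| Rising | 0.076 / 0.060 | 0.100 / 0.100 |
| Plateau | 0.081 / 0.067 | 0.100 / 0.099 |
| Fading | 0.084 / 0.073 | 0.098 / 0.097 |

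In this setting selection outweighs the fading, and all three courses are diluted. The last column is as expected: misses were generated at random given observed scores, where likelihood methods are consistent. It says nothing about misses that depend on the unseen score.

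**4. Power.** Let s be the share of the 3-month change already present at the carried-forward visit. The expected effect is 0.1 × (1 − p(1 − s)). Here 0.1 is read on the SD of change, which is held fixed, and misses are random. At n = 1785 and s = 0.5 the effect is 0.0975, 0.095 and 0.090 for p = 5%, 10% and 20%. Power is 93.8%, 92.4% and 88.9% in place of 95%. At s = 1 nothing is lost.

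**5. Maintenance.** If a mean loss L occurs between T7 and T8 and a random share p of T8 is filled, the apparent loss is (1 − p)L. For L = 0.10 SD and p = 20% this is 0.8 × 0.10 = 0.08 SD. A loss already present at T7 is unaffected.

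**6. The two rules side by side.** Rule 1 is limited to single misses. Rule 2 refers to missed assessments without limit but is tied to recorded reasons. The described query for reasons starts at two consecutive misses. Two readings fit: overlapping rules, or carry-forward for isolated misses with pattern mixture for longer gaps. The text does not choose between them.

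**The case against.** The strongest reply is that the two sentences form a sensible division: carry-forward for an isolated gap, pattern mixture where two or more visits are missed and a reason has been sought. That fits the two-miss trigger and may well be intended. A reader might infer that the plan contradicts itself. The documents do not support that; they leave the scope unwritten, and a separate analysis plan, which the article announces, could supply it. The objection to carry-forward survives on either reading, because the article itself prescribes that method.

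Three further inferences go too far.

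- **That the 3-month result is biased towards no change.** A missed T4 takes the 2-month score, not the baseline. Only a missed T1 takes the baseline, and T1 is not the primary time point. With a plateau and random misses the bias is nil; with fading benefit and random misses it runs upward.
- **That a 12-month loss would be hidden.** It is attenuated: 0.10 shows as 0.08 at 20% filled.
- **That reasons for single misses are not collected.** The article plans to summarise reasons for missed assessments in general. What can be said is that it describes no route to them for a single miss.

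It is also fair that the sizes are modest and rest on assumption. The 20% in the sample-size section is loss to follow-up, not isolated misses, and rule 1 covers only the latter. At 5% filled the random-miss bias is 0.005 SD. An estimate of 0.280 in place of 0.300 would not change the conclusion about benefit. The low coverage at the upper end reflects a small bias set against a very small standard error.

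**Conclusion.** The point holds in this form: carry-forward for single misses is a poor stated choice for a study of change, and the planned model makes it unnecessary. It leans towards the maintenance hypothesis when T8 is missed. At 3 months its direction cannot be known in advance, which is itself a reason not to use it.

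Under random misses with 5% to 20% filled and 0.10 SD still to be gained between T3 and T4, the bias is 0.005 to 0.020 SD against a standard error of about 0.019 SD. It is larger if worse patients miss more. The filled share, course, correlation and missingness pattern are all assumptions. The unstated scope and role of the pattern mixture rule is a secondary gap in wording, not a proven contradiction. This should be fixed before analysis; the sizes do not justify calling it critical.

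**What to change.** 1. Delete the carry-forward sentence.
2. State that the primary analysis is the already planned linear mixed model on all observed assessments, without single imputation, under missing at random.
3. Label the pattern mixture model as a sensitivity analysis, and state which misses it covers.
4. If it is to use reasons, extend the existing project-manager query to a single miss of T4 or T8 where feasible, and treat unrecorded reasons as unknown. A reason item on the next questionnaire would not be enough: no form follows T8, and people who never return would not see it.

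The cost is a wording change in the analysis plan and some extra queries. Intervals will be slightly wider than carry-forward would print. Recruitment was already under way, with 833 participants past baseline by June 2021, so reasons will be unavailable for misses that have already occurred. Steps 1 to 3 do not depend on those reasons being recovered.
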